# **Figure S1**

# **Padres Preparados Jovenes Saludables Program Trial Protocol**

## **Project summary**

Objective: To improve Latino youth (10-14 years) energy balance-related behaviors (EBRBs) (fruit, vegetable, sugar-sweetened beverage, sweets/salty snack and fast-food intakes, physical activity, screen time) by increased frequency of positive paternal parenting practices.

Design: A randomized controlled study with a delayed-treatment control group and randomization at the father-youth dyad. Outcome data will include dietary intake, physical activity/screen time, anthropometric measures, and parenting practice frequency collected at baseline, immediately post, and 3-months post-intervention.

Setting: Community organizations and churches in Minneapolis/St. Paul, MN.

Participants: 40 dyads at each of 6 sites between September 2017-February 2021.

Intervention: An existing 8-week parenting curriculum will be adapted using community-based participatory research principles to promote positive parenting practices (modeling, availability, expectations).

Main Outcome Measures: Youth EBRBs measured with 24-hr dietary recalls/questionnaires, BMI-for-age percentile from measured height/weight. Independent variables include group, time, and group x time interaction.

Analysis: Multiple regression models to test the null hypothesis that changes in outcomes from baseline to immediately post and 3-months post intervention will be the same in intervention and control groups on an intention-to-treat basis. Baseline outcomes, covariates to adjust for baseline differences, potential confounders, and site effect will be included in the models. Statistical significance will be set at p < 0.05, two-tailed.

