**ENVIRONMENT**

Physical/social environmental variables

- **Parenting practices**

- Modeling

- Home availability

- Rules/expectations

- Communication

- General parenting style

Primary: Dietary and physical activity behaviors of youth

Secondary: Frequency of paternal parenting practices

Demographic characteristics

Cultural considerations

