## **Statistical analysis**

During the planning year, focus group interviews will be audio recorded and transcribed verbatim. A codebook will be developed, and transcripts will be coded by two independent project team members. A software program (NVivo v.12, QSR International (Americas) Inc., Burlington, MA) will be used to organize and enable analysis of coded transcripts. Facilitators and barriers to youth EBRBs and parenting practices will be identified using content analysis procedures based on recurring themes.^55^

Father and youth dyads assigned to the intervention condition (n = 120 dyads) will participate in the program immediately, while father and youth dyads assigned to the delayed-control condition (n = 120 dyads) will participate in the prevention program after the 3 months post intervention data collection session. This will allow detection of an effect size of 0.5 standard deviations in sugared-sweetened beverages (SSBs) 24-hr dietary recall with 90% power accounting for a 20% attrition rate (at 3 months post intervention follow-up).

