Demographic characteristics of intervention and control group participants will be compared at baseline using t-tests for continuous variables and chi-square tests for categorical variables to assess whether participant characteristics were equivalent between groups. Adjustments for differences between groups will be done as needed. The primary outcomes, youth EBRBs, BMI-for-age percentile, and BMIz scores, will be evaluated by a multiple regression model (SAS software, SAS Institute Inc., Cary, NC) to test the null hypothesis that immediate post-intervention and 3-month post intervention outcomes are the same in the intervention and control groups. Baseline outcomes, covariates to adjust for baseline differences, potential confounders and site effect will be included in the regression model, to generate least squares adjusted mean changes, to generate a model comparing the intervention to control group. The secondary outcomes, self-reported parenting practices, will be evaluated by ANCOVA models to test the null hypotheses for each of the identified parenting behavior scale scores. Covariates to adjust for baseline differences, potential confounders and site effect will be included in the models to generate least squares adjusted mean changes for each group. A two-tailed significance level (alpha) of 0.05 will indicate statistically significant differences. The response rate expectation at 3 months post-intervention is 80% (based on 20% loss-to-follow up). This expected loss-to-follow up was accounted for in the power analysis for the primary outcome, which is based on 120 families per group. Multi-imputation of missing data is planned for the primary study outcome EBRBs. Chi-square tests and two-sample t-tests will be used to compare baseline characteristics between study completers and those lost to follow up to assess the potential for intervention effect bias due to study dropout. Secondary parenting outcome analyses will only include subjects with parenting practices scales data at the indicated data collection times for each analysis.

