## **Expected outcomes of the study**

**Primary outcome:** The primary outcomes include improvements in youth EBRBs and weight status from baseline to immediate post-intervention and 3 months post-intervention in the intervention compared to control group. Improvements in youth EBRBs include decreased intake of SSBs and sedentary activity and increased intake of fruits, vegetables, and breakfast consumption. The number of youths in the normal weight category according to BMI-for-age weight status categories (5th percentile to less than the 85th percentile) is expected to remain stable over the course of the intervention and the next 3 months.

**Secondary outcomes:** The secondary outcomes include increases in parenting behavior scale scores (parenting practices) between intervention and control parents immediate post-intervention and at 3 months post-intervention. These include making healthy foods and opportunities for physical activity available, role modeling positive EBRBs, setting expectations for improvements in youth EBRBs and improved father-child communication. To observe improvements in these secondary outcomes, fathers are expected to be more involved with their child’s eating and physical activity habits and mealtimes, and to use local resources to support improvements in youth EBRBs.

The project is designed to purposefully engage community organizations and participants based on CBPR^29^ principles in determining their own needs and learning preferences so that materials will be effective and lead to behavior change. The project brings together faculty and staff with relevant research and extension experience working with Latino families.

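### Nine primary outcomes at two visits share one alpha of 0.05 with none designated, although the trial is sized for sugar-sweetened beverage intake only and the outcome lists disagree

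*Protocol*

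**What the plan says.** The Project summary defines youth EBRBs as seven items: "fruit, vegetable, sugar-sweetened beverage, sweets/salty snack and fast-food intakes, physical activity, screen time". The hypotheses under Study goals and objectives cover the same seven, each with a direction, and add stable weight status.

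The Statistical analysis section groups these with two weight measures: "The primary outcomes, youth EBRBs, BMI-for-age percentile, and BMIz scores, will be evaluated by a multiple regression model". The model is meant "to test the null hypothesis that immediate post-intervention and 3-month post intervention outcomes are the same in the intervention and control groups". For significance it gives one rule: "A two-tailed significance level (alpha) of 0.05 will indicate statistically significant differences".

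The sample size paragraph covers a single outcome: "This will allow detection of an effect size of 0.5 standard deviations in sugared-sweetened beverages (SSBs) 24-hr dietary recall with 90% power". It assumes 120 dyads per arm and 20% attrition at the 3-month follow-up. The same section later mentions the power analysis for the primary outcome, in the singular. It also plans multiple imputation for the EBRBs as the primary study outcome, without mentioning BMI.

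Expected outcomes of the study describes the primary EBRBs differently: "Improvements in youth EBRBs include decreased intake of SSBs and sedentary activity and increased intake of fruits, vegetables, and breakfast consumption". Snacks, fast food and physical activity are not named there. Breakfast is added, but neither Tab S2 (assessment measures) nor Tab S3 (food groups) defines a breakfast outcome.

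**The concern.** Nine outcomes are called primary at two visits, each judged at 0.05, and nothing says which result decides whether the trial succeeded. A significant difference on any one of them could be reported as a primary effect. The risk that at least one such claim is false is then well above 5%.

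The sizing statement and the singular reference to a primary outcome suggest that SSB intake was meant to lead, but the text never says so. The differing list under Expected outcomes of the study leaves doubt about which behaviors belong to the primary set. A statistical analysis plan could add a multiplicity adjustment. It would still have to work from a protocol that states the primary outcome in conflicting ways.

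**Working it through.** **Inputs from the Protocol.** Seven EBRBs (Project summary; Study goals and objectives), BMI percentile and BMIz (Statistical analysis), two post-baseline visits, two-sided alpha 0.05, effect 0.5 SD, 120 per arm, 20% attrition. Evaluable per arm: 120 × 0.8 = 96.

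**The plan's own power figure.** Normal approximation: power = Φ(0.5 × √(96/2) − 1.960) = Φ(3.464 − 1.960) = Φ(1.504) = 93.4%. The t-test version gives 93.1%. The stated 90% is therefore slightly conservative. For exactly 90%, 85 evaluable per arm suffice, or 85/0.8 = 107 randomised, against 120 planned. The sample size is adequate for SSB intake at alpha 0.05.

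**Number of tests.** 7 + 2 = 9 outcomes. With each visit tested separately, 9 × 2 = 18 tests. With one joint test over both visits per outcome, 9 tests.

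**Chance of at least one false significant result, either direction, no true effects.**
- 18 independent tests: 1 − 0.95^18 = 60.3%.
- 18 correlated tests, by simulation with 200,000 draws per setting: about 46–57%. The correlations are assumptions, since the Protocol gives none: 0.1–0.3 between outcomes, 0–0.7 between visits, 0.95 between BMI percentile and BMIz.
- 9 independent joint tests: 1 − 0.95^9 = 37.0%.
- The list under Expected outcomes of the study (five EBRBs plus weight status) at two visits, 12 independent tests: 1 − 0.95^12 = 46.0%. With assumed correlations of 0.1–0.2 between outcomes and 0.5 between visits it is about 42–43%.

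**Chance of at least one false result in the hypothesised direction (0.025 per test).**
- 18 independent tests: 1 − 0.975^18 = 36.6%.
- Same assumed correlations: about 24–33%.
- Range: about 24–37%, against 2.5% for one test.

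**Power for 0.5 SD with 96 per arm, by handling of multiplicity (90% sizes by normal approximation).**

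| Handling | Alpha per test | Power (t to normal) | Randomised per arm for 90% |
| --- | --- | --- | --- |
| One designated primary | 0.05 | 93% | 107 |
| Bonferroni over 9 | 0.05/9 = 0.0056 | 74–76% | 132/0.8 = 165 |
| Bonferroni over 18 | 0.05/18 = 0.0028 | 67–68% | 147/0.8 = 184 |

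The planned 120 per arm supports 90% power with one designated primary outcome. It does not under Bonferroni over 9 or 18.

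**The case against.** Several objections have force.

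- **Multiplicity methods are often left to the analysis plan, which is not shown.** True, and the absence of an adjustment formula here is not a defect in itself. But the Protocol itself fixes the set of primary outcomes, the visits and the alpha, and these statements do not fit together.
- **Eighteen tests is only one reading.** This stands. The text describes one regression model per outcome, and the Project summary lists a group-by-time term, so one joint test per outcome is also possible. BMI percentile and BMIz come from the same height and weight, so about eight outcomes are distinct. For weight the expectation is stability, so counting a BMI difference as a benefit is doubtful. The seven EBRBs alone at two visits give 1 − 0.975^14 = 30% for a false benefit if independent.
- **The list under Expected outcomes of the study is introduced as inclusive, so it need not be complete.** Fair. What it leaves out is weaker evidence than what it adds, namely breakfast.
- **Making SSB intake the sole primary outcome is partly a preference, because the stated objective is the whole set of EBRBs.** Also fair. A fixed order or a Holm procedure would control the error too. SSB intake is proposed because it is the only outcome the sample size was justified on.

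Three stronger readings are tempting, and the text does not support them. A reader might infer that a chance success is about as likely as not. The 46–60% range counts differences in either direction, including unfavourable ones, and the figure for a false benefit is 24–37%. A reader might infer that the 5% error rate and the power figure apply to nothing but SSB intake at 3 months. In fact 0.05 holds for each test taken singly, and 0.5 SD gives the same power for any continuous outcome analysed the same way. A reader might also see a further conflict in the framework figure, which has the label "Primary: Dietary and physical activity behaviors of youth". That is scattered text from a conceptual diagram in which child BMI also appears, so it is no evidence of a different outcome set.

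**Conclusion.** The concern holds. The Protocol names nine primary outcomes at two visits under one alpha, designates none, justifies its size on one, refers to the primary outcome in the singular, and gives a second list with an undefined item.

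On the 18-test reading, the chance of at least one false significant result is 60% under independence and about 46–57% under the assumed correlations. The chance of a false benefit is about 24–37%. On the 9-test reading the either-direction figure is 37% under independence. All of these assume no true effect on any outcome. The correlated figures also rest on correlations that the Protocol does not supply. On every reading examined, the overall error rate is far above that of a single test.

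That 3 months is the powered visit is an inference: in the sample size sentence it qualifies the attrition rate, not the comparison.

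**What to change.** Designate youth SSB servings per day, from the 24-hour recalls, as the single primary outcome at one stated visit, tested at two-sided 0.05. The 3-month visit is the natural choice, because the attrition allowance refers to it. Make the other EBRBs, the BMI measures and the immediate post-intervention visit secondary. Handle them in a fixed order, with Holm adjustment, or as estimates with 95% confidence intervals and no significance claims.

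Use one outcome list in the Project summary, Statistical analysis and Expected outcomes of the study. Delete breakfast or tie it to a defined measure, and make the singular and plural references to the primary outcome agree.

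The change needs text only and no additional participants, and SSB power stays at about 93% for 0.5 SD. The cost is that fewer outcomes can be claimed as primary, a real concession given that the objective covers the whole set of EBRBs. If the sponsor prefers to keep several primary outcomes, the error control and the resulting power should be stated together.

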## **Quality assurance**

Weekly meetings among project staff and primary investigators will be held to assure quality. In these meetings, staff will talk about recruitment, program sessions, facilitators, data collection, and data management and report issues that affect recruitment, implementation, and data collection and management to maintain quality. Community partners will also be asked their feedback on sessions and data collections to assure quality.

## **Expected outcomes of the study**

**Primary outcome:** The primary outcomes include improvements in youth EBRBs and weight status from baseline to immediate post-intervention and 3 months post-intervention in the intervention compared to control group. Improvements in youth EBRBs include decreased intake of SSBs and sedentary activity and increased intake of fruits, vegetables, and breakfast consumption. The number of youths in the normal weight category according to BMI-for-age weight status categories (5th percentile to less than the 85th percentile) is expected to remain stable over the course of the intervention and the next 3 months.

**Secondary outcomes:** The secondary outcomes include increases in parenting behavior scale scores (parenting practices) between intervention and control parents immediate post-intervention and at 3 months post-intervention. These include making healthy foods and opportunities for physical activity available, role modeling positive EBRBs, setting expectations for improvements in youth EBRBs and improved father-child communication. To observe improvements in these secondary outcomes, fathers are expected to be more involved with their child’s eating and physical activity habits and mealtimes, and to use local resources to support improvements in youth EBRBs.

The project is designed to purposefully engage community organizations and participants based on CBPR^29^ principles in determining their own needs and learning preferences so that materials will be effective and lead to behavior change. The project brings together faculty and staff with relevant research and extension experience working with Latino families.

Immigrant communities, due to past trauma in their lives, often have a distrust of government and researchers or research practices.^56^ To address this potential issue, the project team will partner with community agencies that are respected in the community. Research materials and language will be carefully crafted with input from the Father Advisory Board to provide information in a respectful manner. The program will be implemented in conjunction with community collaborators using recruitment methods, which have been successful in the past. Therefore, difficulty recruiting the necessary number of father-early adolescent dyads is not expected. However, a higher attrition rate (20%) may occur. The project team will oversample to account for a higher attrition rate, compensate for time, and work with community agencies to implement the program at convenient times as suggested in a previous study involving programming for Latino immigrant families.^57^ The project team will record reasons for dropouts and address issues to enhance retention.

Accuracy of dietary recall by youth is subject to recall bias based on self-reported intake. However, collection of this information over three days (one day in person) using the NDSR multi-pass approach with visual portion-size estimation aids will minimize this error. In addition, parent input will be sought to answer questions about food products.

Participants will be enrolled from organizations in a single Midwestern state, therefore results may not generalize to Latino families in other regions of the US. However, research on Latino father populations in areas of recent settlement are rare, therefore this information may contribute new knowledge regarding how to prevent overweight or obesity in these rapidly growing but under-researched populations. Sampling bias may also occur because participants may have an interest in the subject matter or a higher level of motivation; therefore, results cannot be generalized to a broader group of parents.

Lastly, contamination may occur given that families being served by community organizations may know each other. Because the time investment in the sessions is significant, and sessions build on each other, parents are unlikely to casually share knowledge with other parents or convey substantive knowledge or skills. This issue can be addressed by discussing the problem with all service providers and asking participants to avoid sharing materials.

## **Dissemination of results and publication policy**

Results will be disseminated through the most effective method for the target audiences, including the use of print, video, Spanish language radio/TV broadcasts, web-based and social media technologies in English and/or Spanish. A detailed dissemination plan will be developed with input from the project team and collaborating agencies. This will ensure that information is returned via an effective communication method to the varied stakeholders who have an interest in results (i.e. study participants, collaborating organizations, community professionals, researchers, Extension, educators). Dissemination meetings will be held to present study main outcomes when the study is done.

Results and materials will be disseminated via Extension Just in Time Parenting CoP to which contributions will include webinars, information for the “front page”, and project reports and materials. The project team will also make presentations at scientific meetings and submit articles for publication in appropriate scientific journals.

Publication policy will be developed, and project team members will discuss about the topic and publication ideas and authorship and who will be acknowledge in the weekly meetings.

## **Duration of the project**

See figure 2 for the detailed timeline for the project for each site. In summary, after the baseline data collection tasks are completed by all family members who were participating, father and adolescent pairs will be given an envelope containing a random group assignment into either the treatment group or the waitlisted (delayed treatment) control group. The intervention group will be asked to attend the series of educational sessions the week after baseline data collection. The delayed-treatment control group will be asked to attend the series of educational sessions after the three-month data collection session.

**Fig S2.** Diagram of intervention procedures and timeline.

Weeks

| Treatment group | |  | 1 | 2 | 3 | 4 | 5 | 6 | 7 | 8 |  |  |  |  |  |  |  |  |  |  |  |  |  |  |  |  |  |  |  |  |  |  |
| --- | --- | --- | --- | --- | --- | --- | --- | --- | --- | --- | --- | --- | --- | --- | --- | --- | --- | --- | --- | --- | --- | --- | --- | --- | --- | --- | --- | --- | --- | --- | --- | --- |
|  | | D1 | Education sessions | | | | | | | | D2 | 12-week waiting | | | | | | | | | | | | D3 |  | | | | | | | |
| Delayed-treatment control group | |  |  |  |  |  |  |  |  |  |  |  |  |  |  |  |  |  |  |  |  |  |  |  | 1 | 2 | 3 | 4 | 5 | 6 | 7 | 8 |
|  | D1 | 8-week waiting | | | | | | | | D2 | 12-week waiting | | | | | | | | | | | | D3 | Education sessions | | | | | | | |  |

D1 = baseline data collection session

D2 = post data collection session

D3 = follow-up data collection session

## **Project timeline**

| Key: | * task implemented | | | | | | |  | T – training R - recruitment | | | | | | | | | | | |
| --- | --- | --- | --- | --- | --- | --- | --- | --- | --- | --- | --- | --- | --- | --- | --- | --- | --- | --- | --- | --- |
|  | ! deliverable | | | | | | |  | D - data collection | | | | | | | | | | | |
| Task/Milestones/  Deliverables |  | | | | | | | | | | | | | | | | | | | |
|  | **YEAR 1** | | | | **YEAR 2** | | | | **YEAR 3** | | | | **YEAR 4** | | | | **YEAR 5** | | | |
| QUARTER | 1 | 2 | 3 | 4 | 1 | 2 | 3 | 4 | 1 | 2 | 3 | 4 | 1 | 2 | 3 | 4 | 1 | 2 | 3 | 4 |
| *Project Development* |  |  |  |  |  |  |  |  |  |  |  |  |  |  |  |  |  |  |  |  |
| Recruit/ convene stakeholder team | * | * | * | * |  | * |  | * |  | * |  | * |  | * |  | * |  | * |  | * |
| Hire/assign staff | * |  |  |  |  |  |  |  |  |  |  |  |  |  |  |  |  |  |  |  |
| Finalize project site agreements | * |  |  |  |  |  |  |  |  |  |  |  |  |  |  |  |  |  |  |  |
| Convene collaborators/site representatives | * | * | * |  | * |  | * |  | * |  | * |  | * |  | * |  | * | * | * |  |
| Provide training to collaborators |  | * | * |  |  |  |  |  |  |  |  |  |  |  |  |  |  |  |  |  |
| Develop research protocols | * |  |  |  |  |  |  |  |  |  |  |  |  |  |  |  |  |  |  |  |
| IRB application/ approval | * | * |  |  |  |  |  |  |  |  |  |  |  |  |  |  |  |  |  |  |
| *Formative Research* |  |  |  |  |  |  |  |  |  |  |  |  |  |  |  |  |  |  |  |  |
| Convene parent advisory board | * | * |  |  |  |  |  |  |  |  |  |  |  |  |  |  |  |  |  |  |
| Develop, pilot & finalize curriculum |  | * | * | * |  |  |  |  |  |  |  |  |  |  |  |  |  |  |  |  |
| *Community Implementation* |  |  |  |  |  |  |  |  |  |  |  |  |  |  |  |  |  |  |  |  |
| Sites 1 & 2 |  |  | T | R | D | D | D |  |  |  |  |  |  |  |  |  |  |  |  |  |
| Sites 3 & 4 |  |  |  |  |  |  | T | R | D | D | D |  |  |  |  |  |  |  |  |  |
| Sites 5 & 6 |  |  |  |  |  |  |  |  |  |  | T | R | D | D | D |  |  |  |  |  |
| *Data analysis and reporting* |  |  |  |  |  |  |  |  |  |  |  |  |  |  |  |  |  |  |  |  |
| Data analysis |  |  |  |  |  |  |  |  |  |  | * | * | * | * | * | * | * | * |  |  |
| Final reports written and disseminated |  |  |  |  |  |  |  |  |  |  |  |  |  |  |  |  | * | * | * | ! |
| Report findings to stakeholders, collaborators, participants |  |  |  |  |  |  |  |  |  |  |  |  |  |  |  |  |  |  |  | * |
| Prepare & submit reports for AFRI |  |  |  |  | ! |  |  |  | ! |  |  |  | ! |  |  |  | ! |  |  |  |

